#### Measures

Measures for aim 2 are summarized in Table 2. Research assistants will administer the screener and baseline survey at the time of enrollment in the center. Follow-up assessments at 1 and 3 months will be completed by the counselor via telephone. The 6-month assessment will be completed in-person, at the center, by the research assistant to validate self-reported abstinence. All patient assessments will be administered using REDCap.The primary outcome is the 7-day point prevalence (defined as any smoking, even a puff) carbon monoxide-confirmed (< 8 ppm) smoking abstinence assessed at 6-month follow-up, in line with recommendations from the Society for Research on Nicotine and Tobacco for assessing outcomes in smoking cessation trials [31].Other cessation outcomes: we will include self-reported measures for continuous abstinence between baseline, 3 months, and 6 months; 24-h quit attempts; and reduction in smoking at 1, 3, and 6 months [31].Multi-level mediators and moderators: patient assessments will also collect data on potential mediators (risk perceptions [32], self-efficacy [33], and social norms [34]), and moderators (age, sex, education, cigarettes/waterpipe per day, nicotine dependence [35], and prior quit attempts). Provider assessments will also collect data on center characteristics (e.g., priority, climate) and provider knowledge, attitudes, and self-efficacy [36, 37].Cost: we will collect data on estimates of the time spent delivering the interventions using the provider surveys and counselor electronic logs. We will develop templates to capture these data prospectively and improve cost assessment accuracy. We will assess costs to deliver the interventions, including personnel resources based on MoPH salaries, NRT, educational materials, and technology costs. Costs of developing training materials will also be included. Any hardware and material costs necessary for implementing the interventions will be tracked through invoices. Intervention costs will exclude research costs.

**Table 2 Tab2:** Aim 2 evaluation

	Measures description	Instrument/data source	Timing
Primary outcome	Carbon monoxide-confirmed abstinence	Follow-up patient visit	6 months
Other cessation outcomes	Continuous abstinence, quit attempts, smoking reduction	Phone assessment	1, 3, 6 months
Patient-level mediators	Risk perceptions, self-efficacy, social norms	Phone assessment	0, 1, 3, 6 months
Provider-level mediator	Provider behavior, delivery of AAA, AAC	Patient survey	Index visit
Patient-level moderators	Age, sex, education, cigarettes/waterpipes per day, nicotine dependence, prior quit attempts	Patient survey	Index visit
Clinic- and provider-level moderators	Clinic characteristics (priority, climate), provider knowledge, attitudes, self-efficacy	Provider interview/survey	Pre-trial
Cost	Intervention delivery costs	Cost survey/electronic log	Trial

*AAA* Ask, Advise, Assist, *AAC* Ask, Advise, Connect

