#### Sample size and power evaluation

Justification of the sample size is based on two-level hierarchical mixed-effects logistic regression. The analysis aims to compare the abstinence rate at 6 months post-intervention among the three intervention arms. In this design, the subjects are the level 1 units, and the centers are the level 2 units. All subjects in a particular center receive one of the possible interventions selected at random. Power is evaluated based on the differential effect size between the AAC + NRT and AAC arms, which is expected to be the smallest difference in the abstinence rate. Sample sizes of 480 in the AAC + NRT arm and 480 in the AAC arm, which are obtained by sampling 8 centers per arm with an average of 60 subjects per center, achieve 84% power to detect a difference in the abstinence proportions of 12%. The abstinence proportion at 6 months among AAC + NRT participants is assumed to be 32% under the alternative hypothesis, while the proportion among AAC participants is 20%. The test statistic used is the effect regression coefficient from a mixed-effects logistic regression model. The intra-cluster correlation coefficient is assumed to be 0.01 [29, 30], and the significance level of the test is 0.017 after Bonferroni adjustment. Considering the expected low abstinence rate in the AAA arm and a significant difference compared to both the AAC alone and AAC + NRT arms, and weighing ethical considerations to offer the more intensive intervention when possible, 240 subjects (an average of 30 subjects) per center from 8 centers will be necessary for the AAA arm to achieve more than 85% power with a 0.017 significance level. A total of 1,200 subjects will be necessary: 480 subjects (AAC + NRT; 60 subjects from 8 centers); 480 subjects (AAC; 60 subjects from 8 centers), and 240 subjects (AAA; 30 subjects from 8 centers). Considering a 20% drop-out rate, 1500 subjects will be enrolled.

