#### Analysis

All analyses in aim 2 will account for the multi-level nature of the group-randomized trial (i.e., patients nested within centers). Generalized linear mixed-effects models (GLMM) will form the basis of comparisons across intervention arms, including a random effect for the center. Models of binary outcomes (primary outcome and other cessation outcomes) will use a logit link to estimate relative risks to compare arms; models of continuous outcomes (e.g., quit attempts) will use an identity link assuming a Gaussian distribution, which will be verified to compare means. While balance across arms is expected, we will examine other covariates in the models as necessary, including sex as a biological variable. We will conduct pairwise comparisons to evaluate significant differences between arms, adjusting for multiple comparisons via the step-down Bonferroni method. The multi-level GLMM approach will also be used to evaluate the interventions’ causal direct and indirect effect estimates with mediator variables. Causal mediation analysis will be conducted to decompose the effects of mediators: total effect on the odds ratio scale = direct effect × indirect effect; total effect on the excess relative risk (ERR) scale = direct effect + indirect effect; and proportion mediated on the ERR scale = indirect effect/total effect × 100% using the counterfactual framework [38–42]. SAS CAUSALMED procedure will be used to estimate causal mediation effects. All causal models will include moderator variables. A sensitivity analysis will evaluate if the intervention effects differ by smoking type (cigarettes and waterpipe). The intra-cluster correlation coefficient will be estimated from the final model to inform future research.

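### Six-month continuous abstinence, a secondary outcome, has no CO condition, so a patient who fails the planned 6-month CO test can still count as continuously abstinent

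*Protocol article*

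**What the plan says.** All of this is in the protocol article, under Approach for Aim 2.

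- **Primary outcome (Measures).** It is 7-day point prevalence abstinence, specified as "carbon monoxide-confirmed (< 8 ppm) smoking abstinence assessed at 6-month follow-up".
- **Other cessation outcomes (Measures).** The text states: "we will include self-reported measures for continuous abstinence between baseline, 3 months, and 6 months". No CO condition is attached.
- **6-month contact (Measures).** "The 6-month assessment will be completed in-person, at the center, by the research assistant to validate self-reported abstinence".
- **Earlier contacts (Measures).** "Follow-up assessments at 1 and 3 months will be completed by the counselor via telephone".
- **Table 2.** CO-confirmed abstinence is sourced from the follow-up patient visit at 6 months. The row "Continuous abstinence, quit attempts, smoking reduction" is sourced from a phone assessment at 1, 3 and 6 months.
- **Analysis.** "Models of binary outcomes (primary outcome and other cessation outcomes) will use a logit link to estimate relative risks to compare arms". Continuous abstinence is thus formally compared between arms.

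**The concern.** Being continuously abstinent up to 6 months includes being abstinent in the last 7 days. Among patients assessed at 6 months, one would want everyone counted as continuously abstinent to be a success on the primary outcome as well. The stated definitions do not ensure this: the less demanding state is biochemically checked and the more demanding one is not. Nothing prevents the reported continuous abstinence rate from exceeding the CO-confirmed point prevalence rate.

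What is at stake is the secondary comparison. The article describes no blinding, and patients know whether they receive phone counseling or patches. The 1- and 3-month reports are given to a counselor, and under Table 1 only the AAC and AAC + NRT arms receive phone counseling. The tendency to over-report could therefore differ between arms. If it does, the continuous abstinence contrast can disagree with the primary result for reasons of measurement alone, although a reading that exposes some false claims is already planned.

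**Working it through.** **1. The definitions applied to one patient.** A patient reports no smoking at every contact and has a CO reading of 8 ppm or more at 6 months.

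| Outcome | Criterion in the article | Result |
|---|---|---|
| Primary, 7-day abstinence at 6 months | CO-confirmed, below 8 ppm | Failure |
| Continuous abstinence through 6 months | Self-report | Success |

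No sentence in the article changes the second result.

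**2. The plan's own figure.** No rate or power is stated for continuous abstinence. The only related figure is the 84% power for the primary outcome. Its inputs (Sample size and power evaluation) are 480 patients per arm in 8 centers of 60, intra-cluster correlation 0.01, significance level 0.017, and 32% against 20%.

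- Design effect = 1 + (60 − 1) × 0.01 = 1.59.
- Effective n per arm = 480 / 1.59 = 301.9.
- Two-sided power for two proportions = 83.7%, which agrees with the stated 84%.
- Enrolment = 1200 / (1 − 0.20) = 1500, as stated.

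None of these inputs depends on how continuous abstinence is defined.

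**3. Illustration of the bias.** The true rates are borrowed: "The abstinence proportion at 6 months among AAC + NRT participants is assumed to be 32% under the alternative hypothesis", and "while the proportion among AAC participants is 20"%. They are planning values for 6-month abstinence, not for continuous abstinence. The false-claim rate f, the share of non-abstinent patients who claim abstinence, is my assumption; the documents give none.

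Formula: observed rate = true rate + f × (1 − true rate).

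- AAC + NRT: f = 5% gives 32 + 0.05 × 68 = 35.4%; f = 10% gives 32 + 0.10 × 68 = 38.8%.
- AAC: f = 5% gives 20 + 0.05 × 80 = 24.0%; f = 10% gives 20 + 0.10 × 80 = 28.0%.

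| f in AAC + NRT | f in AAC | Observed rates | Difference (true: 12.0 points) |
|---|---|---|---|
| 5% | 5% | 35.4% vs 24.0% | 11.4 |
| 10% | 10% | 38.8% vs 28.0% | 10.8 |
| 10% | 5% | 38.8% vs 24.0% | 14.8 |
| 5% | 10% | 35.4% vs 28.0% | 7.4 |

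**4. Lower true rates.** Continuous abstinence is the stricter state, so I repeated this with assumed true rates of 15% and 10% (relative risk 1.50). In the same row order, the observed relative risks are 19.3/14.5 = 1.33, 23.5/19.0 = 1.24, 23.5/14.5 = 1.62 and 19.3/19.0 = 1.01 (rates in percent).

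Equal false reporting shrinks the contrast modestly. Unequal false reporting can move it either way, and further.

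**The case against.** The strongest reply is that this is a declared choice. The sponsor made the biochemically confirmed measure primary and openly labelled the others as self-reported. Two outcomes measured by different stated methods may classify a patient differently. A reader might infer that the plan contradicts itself here; it does not. True continuous abstinence implies true 7-day abstinence, but a self-reported version need not be nested within a CO-confirmed one. That part of the reply stands.

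A second reply is that the 6-month visit exists to validate self-report, without restriction to the 7-day measure, and that scoring of discordant readings may be left to an analysis plan that is not shown. This is possible, but the article does name a method for this outcome, and that method is self-report. If an override is intended, one sentence would say so.

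A third reply concerns Table 2. Its source column is shorthand: the mediator row also lists a phone assessment at month 0, although the baseline survey is given in the center. The phone entry therefore does not show a decision to exclude CO. It is a separate, small mismatch.

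A reader might also infer that the outcome will favor the counseled arms. The documents do not support a direction. They give no false-claim rates, and the illustration compares AAC + NRT with AAC, both of which receive phone counseling. It does not quantify a contrast with AAA.

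Finally, one CO reading at 6 months cannot verify abstinence since baseline. That is true, but a failed test does contradict the claim at its end point, and the proposed change relies on no more than that.

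**Conclusion.** The point holds as a weakness in the definition of a secondary outcome. As written, failing the CO test at 6 months does not prevent a patient from being counted as continuously abstinent, and that count enters a between-arm comparison.

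The size of any bias is unknown and so is its sign. With false-claim rates of 5% to 10% and borrowed true rates of 32% and 20%, a 12-point difference could read from 7.4 to 14.8 points. When the false-claim rates are equal it moves by only 0.6 or 1.2 points. These figures rest on assumed false-claim rates and on true rates that the plan states for a different outcome.

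The primary outcome, its power and the sample size are untouched, and nothing in the article makes a trial decision depend on continuous abstinence. This is an inexpensive improvement worth making, not a threat to the main conclusion.

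**What to change.** 1. Define 6-month continuous abstinence as the self-report criterion plus CO below 8 ppm at the 6-month in-person visit. Every assessed patient counted as continuously abstinent is then also a success on the primary outcome.
2. Treat a missing 6-month reading by the same missing-data rule as the primary outcome. The Analysis section already plans multiple imputation for both primary and secondary outcomes.
3. Report the self-report-only version as a sensitivity analysis.
4. Reconcile the phone source given in Table 2 for this outcome at 6 months with the in-person assessment in the text.

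**Cost.** Only wording changes, because the visit and the CO test are already planned. Patients who miss the visit will have no verified value. At the planned 20% drop-out that could be up to 0.20 × 1500 = 300 patients, if all of them miss it. The reading also checks only the end of the abstinence period, and the report should say so.

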#### Analysis

All analyses in aim 2 will account for the multi-level nature of the group-randomized trial (i.e., patients nested within centers). Generalized linear mixed-effects models (GLMM) will form the basis of comparisons across intervention arms, including a random effect for the center. Models of binary outcomes (primary outcome and other cessation outcomes) will use a logit link to estimate relative risks to compare arms; models of continuous outcomes (e.g., quit attempts) will use an identity link assuming a Gaussian distribution, which will be verified to compare means. While balance across arms is expected, we will examine other covariates in the models as necessary, including sex as a biological variable. We will conduct pairwise comparisons to evaluate significant differences between arms, adjusting for multiple comparisons via the step-down Bonferroni method. The multi-level GLMM approach will also be used to evaluate the interventions’ causal direct and indirect effect estimates with mediator variables. Causal mediation analysis will be conducted to decompose the effects of mediators: total effect on the odds ratio scale = direct effect × indirect effect; total effect on the excess relative risk (ERR) scale = direct effect + indirect effect; and proportion mediated on the ERR scale = indirect effect/total effect × 100% using the counterfactual framework [38–42]. SAS CAUSALMED procedure will be used to estimate causal mediation effects. All causal models will include moderator variables. A sensitivity analysis will evaluate if the intervention effects differ by smoking type (cigarettes and waterpipe). The intra-cluster correlation coefficient will be estimated from the final model to inform future research.

Stochastic imputation for handling missing data will be employed as needed [43]. Data analysis with missing data will focus on minimizing bias, maximizing use of available data, and obtaining appropriate estimates of uncertainty. Specifically, we will use intent-to-treat analysis and multiple imputation for the primary outcome, secondary outcomes, and key covariates. Multiple imputations will be applied via PROC MI/MIANALYSE in SAS and several R packages under the missing-at-random (MAR) assumption. We will consider missing data patterns (monotone, univariate, file matching) and variable type (numeric, character) in determining the imputation method. The imputation model will be consistent with our analytic model of the outcomes. If necessary, we will identify potential auxiliary variables to increase the power of our imputation model [44]. Sensitivity analyses will be performed to assess alternative multiple imputation techniques. Finally, several diagnostic statistics and graphical illustrations will be evaluated to assess imputation performance, including a fraction of missing information, relative efficiency, and trace plots.

The cost-effectiveness analysis (CEA) will estimate the incremental cost of delivering the more intensive interventions using cost-per-quit at 6 months as the main outcome. CEA will follow the recommendations of the 2nd U.S. Panel on Cost-Effectiveness in Health and Medicine [45]. Conventional CEA summarizes findings as an incremental cost-effectiveness ratio (ICER) [46]. The ICER estimates the additional resource consumption needed to achieve an increase in an additional unit of effectiveness. The ICER is then compared with a threshold value [47] to determine if the intervention is cost-effective. The net benefit approach calculates the net benefit of an intervention [48, 49]. The strategy that yields the highest net benefit is considered the most cost-effective. Another way to report the results of CEA is cost-effectiveness acceptability curves [50, 51] which estimate the probability that a new intervention yields the largest net benefit. Conventional ICER, net benefit, and acceptability curves will all be reported to facilitate comparison with other CEA in the literature. Although the societal perspective is recommended for CEA [46], our goal is to provide economic data to key stakeholder groups. Therefore, CEA will be conducted separately from the societal and health system perspectives, with appropriate adjustment to the cost measures for each perspective.

### Approach for Aim 3

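### A logit-link mixed model is said to estimate relative risks, but its arm coefficient is an odds ratio (1.88 against 1.60 at the planned rates) and no conversion is stated

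*Protocol article*

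**What the plan says.** The Analysis section for Aim 2 sets the general model: "Generalized linear mixed-effects models (GLMM) will form the basis of comparisons across intervention arms, including a random effect for the center". For binary outcomes, with the primary outcome named explicitly, it continues: "Models of binary outcomes (primary outcome and other cessation outcomes) will use a logit link to estimate relative risks to compare arms". It mentions no log link, no Poisson-type model, no standardisation of predicted risks and no risk difference.

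Under Sample size and power evaluation, the planned test rests on the logistic coefficient itself: "The test statistic used is the effect regression coefficient from a mixed-effects logistic regression model". The planning rates are given there too: "The abstinence proportion at 6 months among AAC + NRT participants is assumed to be 32% under the alternative hypothesis", against 20% in the AAC arm.

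On secondary outcomes, the Measures section for Aim 2 lists among the other cessation outcomes "24-h quit attempts; and reduction in smoking at 1, 3, and 6 months", and Table 2 groups quit attempts in the same way. The Analysis section then says that "models of continuous outcomes (e.g., quit attempts) will use an identity link assuming a Gaussian distribution". The same clause adds that the distributional assumption will be verified.

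**The concern.** The article fixes both a link function and an effect measure for the primary outcome, and the two do not go together directly. With a logit link, the arm coefficient is a log odds ratio. With a center random effect, it is also conditional on center. An odds ratio approximates a relative risk only when the outcome is uncommon, and the trial plans for abstinence of 20% to 32%.

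At stake is how the headline result is read. An analyst who follows the sentence literally could exponentiate the coefficient and report it as a relative risk, so that the benefit of adding NRT would look larger than it is.

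A second, smaller issue sits in the same sentence. Quit attempts are covered by the group described as binary and are also given as the example of a continuous Gaussian outcome, so the text points to two models for one outcome. The article does not define the scale of the measure. A 24-hour quit attempt is naturally recorded as yes or no, or as a small count.

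**Working it through.** **Inputs** (all from Sample size and power evaluation): abstinence 32% in AAC + NRT and 20% in AAC; 480 per arm, as 8 centers averaging 60; intra-cluster correlation 0.01; significance level 0.017; stated power 84%.

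**Reproducing the plan's own figure**
- Design effect: 1 + (60 − 1) × 0.01 = 1.59.
- Effective size per arm: 480 / 1.59 = 301.9.
- Two-sided comparison of 0.32 and 0.20 at level 0.017, normal approximation: power 83.7% (84.3% with unpooled variance), against the stated 84%.

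The article does not state whether the test is one- or two-sided; two-sided reproduces the figure. This confirms that 32% and 20% are the rates the plan was built on.

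**The two effect measures at those rates**
- Odds, AAC + NRT: 0.32 / 0.68 = 0.4706.
- Odds, AAC: 0.20 / 0.80 = 0.2500.
- Odds ratio: 0.4706 / 0.2500 = 1.88.
- Relative risk: 0.32 / 0.20 = 1.60.
- Ratio of the two: 1.882 / 1.600 = 1.18, an overstatement of 18%.
- Apparent relative increase: 88% instead of 60%.

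**Effect of conditioning on center**

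A normal random intercept was integrated numerically so that the marginal rates stay at 32% and 20%. With an intra-cluster correlation of 0.01, on either the latent or the observed scale, the center-conditional odds ratio is 1.89. Conditioning therefore adds almost nothing to the gap.

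**Can the same model give a relative risk?**

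Yes. Averaging the predicted risks of that random-intercept model over the center distribution returns 32% and 20%, and hence a relative risk of 1.60. The model is adequate. What is absent is the step from coefficient to relative risk.

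**Comparisons with AAA**

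The article gives no AAA rate. It says only that AAC + NRT against AAC is expected to be the smallest difference. That puts AAA at no more than about 20% − 12% = 8%. Two assumed values show the range:

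| Assumed AAA rate | AAC vs AAA: RR / OR | AAC + NRT vs AAA: RR / OR |
|---|---|---|
| 8% | 2.50 / 2.88 | 4.0 / 5.4 |
| 5% | 4.0 / 4.75 | 6.4 / 8.9 |

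These figures are illustrative and the conclusion does not rest on them.

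**The case against.** The best defence is that the sentence is incomplete rather than wrong. A logit-link model can yield relative risks through standardised predictions, and the article never says that the exponentiated coefficient will be reported as a relative risk. Its mediation paragraph names the odds ratio scale and the excess relative risk scale separately, so the authors know the difference. The mechanics of conversion could sit in an analysis plan that is not shown.

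Much of this stands. A reader might infer that the trial will certainly publish odds ratios under the name of relative risks; the text does not go that far. What remains is that the article attributes the relative risk to the logit link, while its only stated use of that model's output is the coefficient.

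A reader might also infer that the cost-per-quit analysis would be distorted. The article does not tie that analysis to the model coefficient, and incremental quits can be taken from arm-level quit proportions, so no such harm is shown.

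On quit attempts, the parenthesis about binary outcomes may be loose wording for those cessation outcomes that happen to be binary, since reduction in smoking is in the same list. The promise to verify the Gaussian assumption also counts in the plan's favour. Checking a distribution does not settle which of two models applies, however, so this smaller inconsistency stays.

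**Conclusion.** The concern holds as a mismatch between the stated link and the stated effect measure for the primary outcome. At the plan's own 32% and 20%, confusing the two would turn 1.60 into 1.88, an 18% overstatement of the ratio. The gap depends on the rates: it shrinks if observed abstinence is much lower in both arms and widens if it is higher at a similar relative risk.

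Nothing in the design is affected. The null hypothesis of no difference between arms is the same on either scale, so the test, the multiplicity adjustment, the 84% power and the 1500 enrolled do not change. This is a correction to make before analysis, not a flaw that threatens the trial. The quit-attempt inconsistency is real but minor, and it concerns a secondary outcome only.

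**What to change.** 1. Keep the mixed logistic model for the hypothesis test and label its exponentiated coefficient an odds ratio, conditional on center.
2. State how the relative risk and the risk difference will be obtained. One route is marginal standardisation of predicted risks from the same model, with delta-method or other intervals that allow for only 8 centers per arm. A bootstrap that resamples so few centers is a doubtful choice. The alternative is a log-link modified Poisson model with cluster-robust standard errors corrected for the small number of centers.
3. Define the quit-attempt measure and give each version one model: any 24-hour attempt (yes or no) under the binary model, and the number of attempts, if it is used, under a count model. Reserve the Gaussian model for outcomes that are actually continuous.

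The cost is a few sentences in the analysis plan and a few lines of code. No change to design, sample size or data collection follows from items 1 and 2. For item 3, it should be confirmed that the follow-up questions record quit attempts in the form chosen. The Data Availability statement says that no data had been collected at publication.

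### For three pairwise arm comparisons, step-down Bonferroni is valid, but Shaffer's step-down procedure never rejects less at the same familywise error: a free, small improvement, not an error

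*Protocol article*

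**What the plan says.** The Analysis section under Aim 2 states: "We will conduct pairwise comparisons to evaluate significant differences between arms", and fixes the multiplicity method as "adjusting for multiple comparisons via the step-down Bonferroni method". Step-down Bonferroni is Holm's procedure. With three tests and a 5% familywise level, the ordered p-values are compared with 0.05/3, 0.05/2 and 0.05. The article does not print these thresholds; they follow from the name of the method.

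The section Sample size and power evaluation uses the single-step level: "the significance level of the test is 0.017 after Bonferroni adjustment". It reports 84% power for AAC + NRT (32%) versus AAC (20%), and more than 85% power for the AAA comparisons. For AAA it gives no rate, only "Considering the expected low abstinence rate in the AAA arm".

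**The concern.** Holm's procedure is built for any set of hypotheses and makes no use of how they relate. Here they are related. If AAC + NRT and AAA truly differ, AAC cannot equal both of them, so at most one null is left to protect after the first correct rejection. The middle threshold of 0.025 guards against two remaining true nulls, which cannot occur.

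AAC + NRT versus AAA will nearly always give the smallest p-value. Any cost of the middle step then falls on the other two comparisons: the added value of NRT, on which the trial is sized, and the value of phone counseling over standard care. At stake is a little power on those two questions, which can be recovered without patients, data or error rate.

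**Working it through.** **Inputs.** From Sample size and power evaluation: 32% (AAC + NRT) and 20% (AAC); 8 centers per arm; 60, 60 and 30 analysed patients per center (AAC + NRT, AAC, AAA); ICC 0.01; level 0.017. Assumed: two-sided tests, familywise level 0.05 (inferred from 3 × 0.017 = 0.051), and the AAA rate, which is varied.

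**Step 1. Reproduce the stated power.**
- Design effect = 1 + (m − 1) × ICC. For m = 60: 1 + 59 × 0.01 = 1.59. For m = 30: 1 + 29 × 0.01 = 1.29.
- Effective n per arm: 480/1.59 = 301.9 and 240/1.29 = 186.0.
- Power = Φ{[d√n − z√(2p̄(1 − p̄))] / √(p₁(1 − p₁) + p₂(1 − p₂))}, with d = 0.12, p̄ = 0.26 and z = 2.387 for two-sided 0.017.
- This is Φ{(2.085 − 2.387 × 0.620)/0.614} = Φ(0.98) = 83.7%, which matches the stated 84%. The sample size therefore does not rely on any step-down gain.

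**Step 2. AAA rates compatible with the plan.** At 0.017, power for AAC versus AAA is 90.4% if AAA is 8% and 82.3% if it is 9%. It crosses 85% near 8.7%. The claim of more than 85% power therefore implies an AAA rate of about 8.7% or lower.

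**Step 3. Why Shaffer's thresholds are valid.** Any two of the three pairwise nulls together imply the third. The closed family therefore contains only the global null and the three single nulls. Test the global null by smallest p ≤ 0.05/3, then each single null at 0.05. That gives 0.05/3, 0.05, 0.05 with strong 5% control. No threshold is below Holm's, so every Holm rejection is also a Shaffer rejection. The two differ only when the smallest p-value passes 0.05/3 and the next lies above 0.025 and at or below 0.05.

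**Step 4. Familywise error, simulated.** With all three rates equal at 20%, it is about 4.3% (normal approximation) to 4.5% (center-level t-tests) for both procedures. With AAC + NRT = AAC = 20% and AAA = 8%, that true null is rejected about 5.0% of the time under Shaffer and about 4.2% under Holm (normal approximation).

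**Step 5. Power for AAC + NRT versus AAC, Holm to Shaffer.** The normal column simulates arm estimates with the effective sizes above. The 14-df column simulates beta-binomial center data and tests center means.

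| AAC + NRT / AAC / AAA | Normal | 14-df t |
|---|---|---|
| 32/20/5% | 92.1 to 92.1 | 88.3 to 88.4 |
| 32/20/8% | 92.1 to 92.1 | 87.7 to 88.1 |
| 32/20/12% | 90.9 to 92.1 | 84.9 to 88.1 |
| 28/20/12% | 58.5 to 63.1 | 50.7 to 57.0 |

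At the edge of the planning range (AAA 8.7%) the 14-df result is 87.6 to 88.4. In the last row, a normal reference applied to the simulated center data gives 59.6 to 63.6, so the gain runs from about 4 to about 6 points. For AAC versus AAA at 28/20/12% the 14-df result is 54.2 to 60.9. In the simulations Shaffer rejected whatever Holm rejected.

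**The case against.** The strongest reply is that nothing here is wrong. Step-down Bonferroni is a standard, pre-specified method with strong familywise control. The 84% reproduces at the stricter 0.017, and sizing on the single-step level while analysing step-down is merely conservative, not contradictory. All of that stands, and it is why this is not raised as an error.

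A reader might infer that the trial gives away meaningful power. The documents do not support that. Under their own assumptions the difference is below one point, and with a low AAA rate Holm already lifts power for AAC + NRT versus AAC to about 88 to 92%. The larger gains need assumptions outside the plan. An AAA rate of 12% leaves AAC versus AAA with well under the stated 85% power at 0.017, and 28% versus 20% replaces the 12-point difference with 8 points. In that last case power for the key comparison is inadequate under either procedure.

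A reader might also infer that both remaining comparisons are held to 0.025. They are not: once the smaller of the two passes 0.025, Holm tests the last at 0.05.

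The size of the gain also depends on the reference distribution. The article plans a mixed model with a center random effect, not separate t-tests on 14 df, so the upper figures describe one reading of a design with 8 centers per arm.

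The argument that this is detail for the SAP carries less weight. The article already names the method, and the proposal replaces that named method with one that is never worse.

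**Conclusion.** The point holds as a free improvement. For three pairwise comparisons of three arms, Shaffer's procedure dominates the planned one at the same 5% familywise level. The gain for AAC + NRT versus AAC is:
- 0 to about 0.9 points under the planning assumptions;
- about 1 to 3 points at an assumed 32/20/12%;
- about 4 to 6 points at an assumed 28/20/12%.

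The last two ranges run from a normal to a 14-df reference. They rest on assumed AAA rates (the article states none), a two-sided 5% familywise level, ICC 0.01 and equal center sizes within each arm. The dominance itself rests on none of these rates. It needs only that the family is the three pairwise comparisons of one outcome and that each pairwise test holds its own level.

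**What to change.** In the Aim 2 Analysis section, replace the named step-down Bonferroni method with Shaffer's logically constrained step-down procedure for the three pairwise comparisons: 0.05/3 for the smallest p-value, then, if it is rejected, 0.05 for each of the other two. Leave 0.017 in Sample size and power evaluation as the conservative sizing level. The cost is one phrase, fixed before outcome data are seen. It needs no extra patients or data, and familywise control stays at 5%.
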